### Sample size

The sample size is based on one of the two primary outcome variables, Neck Disability Index (NDI) and Global Perceived Effect (GPE). The GPE is chosen, because this outcome variable needs the largest group of participants. Previous studies have shown that the effect of manual therapy on GPE is 68.3% [13] and 70.1% [18].

A 20% difference on the GPE scale is considered clinically relevant. Based on α = .05 and an 80% power (β = 0.2) 76 participants per intervention group are required.

With regard to prospective drop outs (15%), 90 participants per group will be recruited in this trial. A similar sample size was used in previous research [19,34,35].

### Interventions

#### MTU (experimental intervention)

During the first consultation the manual therapist enquires about the complaints of the patient. The manual therapist conducts a number of measurements according to protocol, thus registering the natural asymmetry in form, posture and movement (see figure 1).

**Figure 1 F1:**
[figure not shown]
**Shows the differences of the intervention between the experimental group MTU (Manual therapy Utrecht) and the control group PT (physical therapy)**.

By means of an interpretation according to the protocol the measurements are translated into preferred movements in the patient's joints. During treatment these preferred movements are executed by the manual therapist in the patient's joints. The treatment techniques used by the manual therapist are very gentle mobilizations, without high velocity thrust techniques and are in general painless. In MTU it is common to give advice and recommend exercise.

A treatment session lasts between 30 and 60 minutes. In this trial treatment is repeated after one or two weeks. The maximum number of sessions is six.

The manual therapist has a minimum of five years of working experience.

#### Physical therapy (comparison intervention)

At the first appointment the physical therapist enquires about the complaints. The physical therapist conducts a complaint related function examination, after which treatment goals are determined. Treatment can consist of active exercises, manual traction or stretching and massage. The aims of exercises are improvement of strength, mobility and movement coordination. Specific manual mobilization techniques, known as manual-therapeutic techniques, are not a part of physiotherapeutic treatment. Treatment sessions take place no more than twice a week with a maximum of nine sessions; session duration is approximately 30 minutes. In each session the physical therapist will spend a minimum of twenty minutes on active exercise therapy combined with instruction.

To prevent overlap with MTU, physical therapists are selected who are not (also) trained as manual therapists or have started this training.

The physical therapist has at least five years of working experience.

Figure 1 contains the description of the experimental and control intervention.

#### Co-interventions

During the intervention period of the trial, participants will not receive treatment other than the ones allocated. Patients are free to use medication prescribed either by a physician or of their own choice. Participants are allowed to withdraw from the treatment at any time. Continuation of the treatment and co-interventions are registered.

### Outcome

In the choice of primary and secondary outcome the ICF (International Classification of Functioning, Disability and Health) components have been taken into account. These cover the following categories: bodily functions, anatomical properties; activities and participation; external factors; personal factors [36].

#### Primary outcome

Global Perceived Effect (GPE) measures overall improvement or worsening. Measuring of GPE will be done by scoring a 7-point ordinal scale (ranging from much worse to complete recovery) [37,38]. The GPE measures patient subjective global improvement and has a high face validity [39]. In routine clinical practice it is important, since it would not make sense to classify a patient as improved or deteriorated against the patient's own personal assessment [39,40]. Functioning is the second primary outcome. The Neck Disability Index Dutch Version (NDI-DV) is a questionnaire containing 10 items. All items are related to daily functioning and functions. The maximum score is 50; the higher the score the more limitations. Validity and reliability of the NDI are good [41,42] and so is the responsivity [42-44].

#### Secondary outcomes

To assess neck pain intensity the Numeric Rating Scale (NRS) will be used. This scale (11 points) measures the pain intensity experienced by the patient in the previous week. Dalton et al argued for standardization of pain measuring by means of the 11-point Numeric Rating Scale (NRS) [45]. The Visual Analogue Scale (VAS) and the NRS are the most cited pain measures, largely because they are simple to use. The NRS is a sensitive instrument, comparable with the VAS [46,47] or more sensitive than the VAS [48]. The NRS has been chosen on the basis of administrative aspects rather than for statistical power. It has been proved to be more comprehensible for patients [45-47,49,50]. Also the NRS is valid for verbal patient questioning [51].

The general health questionnaire (SF36) will be used to put together a detailed health profile on the basis of scores on eight health dimensions as well as a sum score on both physical and mental health [52].

The EuroQol5D is a standardized, non-disease-specific instrument for describing and valuing health states. It has the additional possibility of converting the descriptive data into values for economic (cost-effectiveness) analysis by linking patients' health state descriptions to empirical valuations of health states obtained from the general population [53]. EuroQol5D is simple to use, valid, responsive to change and reliable instrument for group comparisons [54-56]. The EuroQol5D is a two-part instrument. Part one records self-reported problems on each of five 'domains': mobility, self-care, usual activities, pain/discomfort and anxiety/depression. Each domain is divided into three levels of severity corresponding to no problem, some problem and extreme problem. Part two of the questionnaire records the subject's self-assessed VAS rating of health.

Participants are to fill in questions about (partial) disablement/return to work (if applicable), use of analgesic (types of and quantities), medical consultation during treatment and follow/up, costs and side effects [57,58].

The patient will fill in the questionnaires at baseline, 3, 7, 13, 26, 39 and 52 weeks after treatment has started (see table 1).

**Table 1 T1:** Timing of measurements

measurements	Baseline T0	T3	T7	T13	T26	T39	T52
In- and exclusion	X						

Demographic data	X						

GPE		X	X	X	X		X

NDI-DV	X	X	X	X	X		X

NRS pain	X	X	X	X	X		X

SF-36	X		X				X

Side effect		X	X	X			

EuroQol5D		X	X	X	X	X	X

Costs		X	X	X	X	X	X

GPE = Global Perceived Effect (7-points scale); NDI-DV = Dutch version Neck Disability Index; NRS = Numeric Rating Scale for pain; SF36 = short form -36 quality of life questionnaire

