### Trial Objectives

The primary objective is to compare the short-term effectiveness (7 weeks) and long-term effectiveness (52 weeks) of MTU with physical therapy in patients with sub-acute and chronic neck pain with regard to global perceived effect, functioning and pain.

The cost-effectiveness of manual therapy compared with physiotherapy will also be evaluated.

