#### Multi-variate analysis

An ANOVA will be used to analyze differences between conditions per person (within subject) and per group (between groups).

Descriptive statistics will be applied to make a comparison between the baseline data of the manual therapy and the physical therapy groups and to assess whether the randomisation has been successful. Group differences between the interventions with a 95% confidence interval will be calculated for all outcome measures.

The statistical analyses will be carried out according to the intention-to-treat principle, whereby the patients are analysed in the intervention group in which they were originally placed. The differences between groups will be tested by ANOVA/mixed model (continuously) and by the Chi-Square test for dichotomous variables.

Multi-variate regression analysis will be used to test the influence of the baseline variables on the outcomes.

For the primary outcome measure Global Perceived Effect (GPE) a selection can be made between responders (positive effect) and non-responders (no or negative effect) to the treatment received.

The data will be processed by SPSS/SAS statistical software.

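### Table 1 schedules no baseline EuroQol5D, so the utility comparison behind the cost-effectiveness objective cannot be adjusted for its own starting value

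*Protocol article*

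**What the plan says.** Protocol article, Trial Objectives: "The cost-effectiveness of manual therapy compared with physiotherapy will also be evaluated".

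Protocol article, Secondary outcomes, on EuroQol5D: "It has the additional possibility of converting the descriptive data into values for economic (cost-effectiveness) analysis". No other instrument is given this role. The SF-36 is described only as a health profile with physical and mental sum scores.

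The same section gives the timing: "The patient will fill in the questionnaires at baseline, 3, 7, 13, 26, 39 and 52 weeks", counted from the start of treatment, with a reference to Table 1. The table header has seven time columns: "measurements Baseline T0 T3 T7 T13 T26 T39 T52". The EuroQol5D row has six marks, "EuroQol5D X X X X X X", which stand under T3, T7, T13, T26, T39 and T52. The T0 cell is empty. NDI-DV, NRS pain and SF-36 each have a T0 mark.

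Protocol article, Multi-variate analysis: "Multi-variate regression analysis will be used to test the influence of the baseline variables on the outcomes".

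**The concern.** An empty T0 cell is natural for GPE, side effects and costs, which exist only once treatment has begun. It is not natural for a measure of current health, which has a value before treatment and is normally related to later values. The EuroQol5D row has exactly the same marks as the costs row, so the gap may have come from treating the two as one economic block.

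If the schedule is followed as printed, the first utility is taken when patients are already three weeks into a six-week treatment. The pre-treatment EuroQol5D is then never observed, and no later analysis plan can supply it. Both arms receive an active therapy, so the utility difference may well be small. Precision and protection against an unlucky baseline split therefore matter for the economic objective.

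**Working it through.** The plan states no figure on this point, so there is none to reproduce. The check has three parts.

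**1. Is the empty cell real?** Matched to the header, the rows for GPE, NDI-DV, SF-36, EuroQol5D and costs each have seven time cells.

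| Row | T0 | T3 | T7 | T13 | T26 | T39 | T52 |
|---|---|---|---|---|---|---|---|
| NDI-DV | X | X | X | X | X | | X |
| SF-36 | X | | X | | | | X |
| EuroQol5D | | X | X | X | X | X | X |
| Costs | | X | X | X | X | X | X |

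The EuroQol5D row is complete, with all six follow-up cells filled, so it has not lost or shifted a mark. No other section schedules a baseline EuroQol5D.

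**2. How much of the year is affected directly?** Suppose utility is summarised as an area under the curve by the trapezoidal rule over 0-52 weeks. This is an assumption, as the article names no method.

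- Share of the year in weeks 0-3: 3/52 = 5.8%. The remaining 49/52 = 94.2% lies between scheduled measurements.
- Weight of a T0 value: (3/2)/52 = 1.5/52 = 2.9%.
- With T0 added, the weights are 0.029 (T0), 0.067 (T3), 0.096 (T7), 0.183 (T13), 0.250 (T26), 0.250 (T39) and 0.125 (T52).

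The missing stretch is small. If both arms are given the same starting value, its contribution is equal in both and cancels from the difference.

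**3. What does losing the covariate cost?** The documents give neither a utility SD nor a correlation, so both are assumed. The group sizes, 76 required and 90 recruited per arm, come from the Sample size section.

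- Precision: adjusting for a baseline with correlation r to the outcome multiplies the variance by 1 − r².
  - r = 0.4: variance falls by 0.16 (16%); SE factor √0.84 = 0.917, a fall of about 8%.
  - r = 0.5: variance falls by 0.25 (25%); SE factor √0.75 = 0.866, a fall of about 13%.
- Chance imbalance: SE of the baseline difference = SD × √(2/n).
  - SD 0.20, n = 90: 0.20 × √(2/90) = 0.030.
  - 95% half-width at the low end (SD 0.15, n = 90): 1.96 × 0.0224 = 0.044.
  - 95% half-width at the high end (SD 0.30, n = 76): 1.96 × 0.0487 = 0.095.
- Carry-over into the outcome difference: slope × imbalance, where slope = r × SD(outcome)/SD(baseline).
  - With equal SDs of 0.20, a one-SE imbalance carries 0.4 × 0.030 = 0.012 to 0.5 × 0.030 = 0.015.
  - The SE of the outcome difference is then also 0.030, so the shift is 0.4-0.5 of one standard error.
  - If a year-averaged utility has a smaller SD than a single baseline value, the shift in utility units is smaller.

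This carry-over is not a further error. It is part of the sampling variation that the unadjusted standard error already counts. Adjustment would remove it.

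**The case against.** **Randomisation.** Expected baseline utility is equal in the two arms, so the unadjusted comparison is unbiased and its confidence interval is honest. Pre-stratification on main-complaint score and age limits imbalance further. This stands. A reader might infer that the utility result will be biased, but the documents do not support that.

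**Adjustment by proxy.** SF-36, NDI-DV and NRS are all marked at T0, and the article plans regression on baseline variables. It is tempting to say that utility cannot be baseline-adjusted at all. That goes too far: only adjustment for EuroQol5D itself, and change from its own baseline, are lost. The gain from a T0 EuroQol5D beyond these proxies is smaller than the 8-13% above.

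**Text against table.** A reader might see the sentence that lists baseline as contradicting the table. It does not. It gives all visits for the questionnaires together and defers to Table 1. It also lists week 39, when only EuroQol5D and costs are marked. It promises no baseline EuroQol5D.

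**QALYs.** The article never mentions QALYs and does not name the effect measure for cost-effectiveness. It says only that EuroQol5D offers the possibility of "converting the descriptive data into values for economic (cost-effectiveness) analysis". A QALY analysis is a reasonable inference from that role, but it remains an inference.

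**A slip.** The empty cell may be a typesetting error. That cannot be excluded. If so, the remedy is to correct the table.

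What remains is that the printed schedule looks complete, omits the pre-treatment value of the one instrument with an economic role, and cannot be repaired for a patient once treatment has started.

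**Conclusion.** The point holds as a weakness of the measurement schedule. As printed, change in EuroQol5D utility from baseline cannot be computed, 5.8% of the year has no starting value, and the utility comparison can be adjusted only for proxies. The comparison stays valid. With an assumed correlation of 0.4-0.5, the loss is a forgone 16-25% reduction in variance (about 8-13% in standard error), and less after proxy adjustment.

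The point should be fixed, but it does not threaten the trial. EuroQol5D is a secondary outcome, and the primary outcomes (GPE and NDI-DV) and the sample size are untouched. The empty cell is read directly from Table 1. The sizes rest on an assumed correlation, an assumed utility SD and an assumed area-under-the-curve summary.

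**What to change.** 1. Establish whether EuroQol5D is already completed at T0. If it is, correct Table 1; nothing else changes.
2. If it is not, mark EuroQol5D at T0 and collect it with the other baseline questionnaires before the patient learns the allocation. Estimate the between-group difference in utility (or QALYs, if used) by regression with T0 utility as a covariate.
3. Recruitment began in September 2008, so some patients may already lack the value. For them, adjust for the T0 SF-36 and the other baseline scores, and use one common starting value in both arms for weeks 0-3. The SF-36 scores can enter as covariates directly, so no mapping to utility is needed; the article gives none. State this rule before the data are compared by arm.

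The cost is five items and one VAS added to a baseline pack that patients already complete, a slight extra burden, and a short amendment during recruitment. The amendment cannot restore T0 values for patients already treated, so the gain grows the sooner it is made.

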**Figure 2 F2:**
[figure not shown]
**NECKproject flow chart**.

The LRA schedules an appointment with the patient. The patient will be informed again by the LRA about the contents and objectives of the study. After this, the LRA conducts a diagnostic examination according to protocol. Training and an instructional DVD is provided by the NECKprojectgroup to the LRA to ensure a correct intake procedure.

The purpose of the intake procedure is to assess inclusion and exclusion criteria. Should the patient be eligible, he/she is informed about how to fill in the questionnaires either digitally or on paper. After signing the informed consent, randomisation takes place. The patient receives an envelope with the name and address of the (local) therapist that will provide the treatment. The patient makes an appointment with the therapist in attendance and starts treatment. The LRA has no further contact with the patient in relation to this trial.

All questionnaires are sent either digitally or by mail to the central blinded investigator.

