#### Randomisation, blinding and allocation

Block randomisation will take place through the computer after pre-stratification on the basis of prognostic aspects for the complaints: level score of the main complaint (scale 10: <7 or ≥ 7) and age (< 40 or ≥ 40 years) [59,60].

Four groups are formed which are randomized for both intervention groups. The randomisation scheme will be generated by the central computer. The LRA is blinded for the randomisation.

Treatment with physical therapy and MTU will take place at different locations. The investigator in charge of the database has no access to the key of the combination patient data - research number - treatment allocation. In the case of missing data the computer system will automatically generate an email to the participant directly or to the secretary of the NECKprojectgroup. The computer or secretary will send the patient a standard reminder. None of the therapists know the patient number(s).

The data from the questionnaires filled in digitally on http://www.neckproject.nl are sent directly to the database of the central researcher. The researcher is blinded from patients' data and type of intervention. The questionnaires filled in by hand are sent to a central freepost address. These lists are entered into the database by a secretary. Loss of data should be prevented by actively reminding the patient by email, mail or telephone.

Patients who fill in the forms digitally will automatically receive a reminder by email. Patients who fill in the lists by hand will receive them through the post. The secretary will attend to this.

Each treatment sessions will be registered by using standard forms filled in by the therapist. By doing spot checks the information received about the content of the treatment session will be inspected by the researcher from the UMC St Radboud.

Visitations will take place to ensure the therapists in attendance are keeping to the research protocols.

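### Follow-up is timed from the start of treatment, not from randomisation: patients who never start have no outcome dates under intention to treat, and time since randomisation can differ by arm

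*Protocol article*

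**What the plan says.** Methods/Design, Secondary outcomes, sets the schedule for all questionnaires: once at baseline, then at "3, 7, 13, 26, 39 and 52 weeks after treatment has started". Table 1 places the two primary outcomes, GPE and NDI-DV, at T3, T7, T13, T26 and T52 (NDI-DV also at T0). Trial Objectives names 7 and 52 weeks as the short-term and long-term comparisons.

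The Recruitment section gives the order of events. "After signing the informed consent, randomisation takes place". Next, "The patient receives an envelope with the name and address of the (local) therapist that will provide the treatment". Then, "The patient makes an appointment with the therapist in attendance and starts treatment". No limit is stated on the time between randomisation and the first session.

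Randomisation, blinding and allocation adds: "Treatment with physical therapy and MTU will take place at different locations". Co-interventions lets participants withdraw from treatment whenever they wish. Under Statistics, Multi-variate analysis: "The statistical analyses will be carried out according to the intention-to-treat principle", with each patient kept in the group of original placement.

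**The concern.** The time origin is an event that happens after randomisation, once the allocation is known, and whose timing depends on the patient and on the allocated therapist's availability. That raises two separate problems.

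The first is logical. An intention-to-treat analysis needs outcomes from every randomised patient. A schedule counted from the start of treatment gives no date to a patient who never starts. If such patients are not followed, the analysed set depends on something that happened after allocation, and the reasons for not starting may differ between manual therapy and physical therapy.

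The second is a possible bias. If one arm waits longer for its first session, its patients have lived longer with the complaint since randomisation when they fill in the form for a given week. Where the complaint tends to improve over that time, the arm with the longer wait gains on GPE and on NDI change for a reason unrelated to treatment.

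**Working it through.** **The passages side by side.** The sequence is: intake, instruction on the questionnaires, consent, randomisation, envelope, appointment made by the patient, first session. The clock starts at the last step, while the analysis population is fixed at randomisation. For a patient whose first session comes w weeks after randomisation, the form for week t is completed w + t weeks after randomisation. For a patient with no first session, w does not exist, so neither does w + t. This needs no assumed figure.

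**Difference between arms.** At nominal week t the arms differ in mean time since randomisation by w(MTU) − w(PT). If the responder percentage is changing by r points per week, the comparison shifts by about r × [w(MTU) − w(PT)]. The article gives neither w, so the shift cannot be computed. Only r can be bracketed, and only roughly.

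**Illustration of r.** Research in the Netherlands cites an earlier trial with perceived recovery at 7 weeks of 68% (manual therapy) and 51% (physical therapy), and 72% and 63% at one year.

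- Average change from week 7 to week 52: physical therapy (63 − 51)/45 = 0.27 points per week; manual therapy (72 − 68)/45 = 0.09.
- Upper bound before week 7, assuming a straight rise from 0%: physical therapy 51/7 = 7.3 points per week; manual therapy 68/7 = 9.7.

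For an assumed one-week difference in mean wait, the shift is then about 0.1 to 0.3 points at week 52. At week 7 it lies anywhere from that size up to about 7 to 10 points. The difference regarded as clinically relevant under Sample size is 20 points. The upper bound is generous: those patients were being treated, whereas the extra time here would be spent waiting.

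**Never-starters.** The planned size is 76/(1 − 0.15) = 89.4, rounded up to 90 per group, or 180 in all. No never-starter rate is given. Assumed rates of 2%, 5% and 10% give 180 × 0.02 = 3.6, 180 × 0.05 = 9 and 180 × 0.10 = 18, so about 4, 9 and 18 randomised patients without defined visit dates.

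The sample size itself does not depend on the time origin.

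**The case against.** The best defence is that counting from treatment start is a reasonable choice. Treatment lasts six weeks, so week 7 on that clock assesses both arms just after treatment ends. On a randomisation clock, unequal waits would still matter: the arm that waits longer would be assessed with less treatment received. This is true, but the imbalance then becomes part of what being allocated to that therapy entails, instead of a difference in when patients are measured. It also leaves the never-starter problem unanswered.

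It can also be said that nothing excludes never-starters. Forms pass between the patient and the central system, with reminders, and patients are kept as placed. That shows they could be followed, but the only schedule stated still gives them no date. This is a stated rule that conflicts with another stated rule, not a detail left out of an article.

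Two further objections stand and limit the point. No passage shows that waits differ; different locations make it possible, no more. And natural improvement is not uniform across eligible patients: the Background says that discomfort lasting six months or longer stays fairly stable on average, while the entry criteria admit episodes of up to 52 weeks.

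A reader might also infer that baseline questionnaires are completed after the allocation is known, since the text says only that "he/she is informed about how to fill in the questionnaires either digitally or on paper" before it turns to consent and randomisation. The documents do not support that. Table 1 puts the eligibility check in the same T0 column as the baseline questionnaires, and eligibility is settled at intake before randomisation. The main-complaint score used for stratification must also be known beforehand. The flow chart that may settle the order is not available in the text reviewed.

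**Conclusion.** The point holds in two parts of different strength. That a randomised patient who never starts has no defined follow-up dates, in conflict with the intention-to-treat analysis, follows directly from the text and rests on no assumption. How many patients this would affect is unknown.

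That time since randomisation can differ by arm is a possibility the design leaves open. A reader might infer that the comparison is already biased towards one therapy. The documents do not show this: it would need unequal waits together with real change over the waiting time, and a delay of equal length in both arms would produce no bias by this route. If waits do differ, the effect would fall mainly on weeks 3 and 7. On the cited rates, the 52-week comparison would move by only a fraction of a point per week of difference. The bracket shown for week 7 is an illustration, not an estimate.

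**What to change.** Schedule T3 to T52 from the date of randomisation for every randomised patient, whether or not treatment starts. Record the date of the first session and report the interval from randomisation to first session by arm. If the sponsor prefers to keep the treatment-start clock, the minimum is to give patients who never start follow-up dates counted from randomisation, and still to report the interval by arm.

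The cost is a short amendment and a changed setting in the reminder system. Because randomisation is done by the central computer, its date should be available for everyone. There are two downsides. A late starter's week-7 form may fall before the six-week treatment period ends, which the recorded start dates would allow the report to describe. And recruitment began in September 2008, so patients already enrolled would stay on the old schedule; the report should say which schedule each patient followed.
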